### **3.5 General principles for reporting and analysis**

The following general principles for reporting and analysis will be used:

- 5% two-sided level of statistical significance, with corresponding 95% confidence intervals presented where applicable.
- No adjustments for multiplicity are planned.
- Summary statistics will include either mean, standard deviation, and/or median, interquartile range.
- Treatment groups will be labelled in the tables as Intervention Group and Control Group accordingly, and a total column will be included in tables where applicable.

## **4 Planned analyses and reporting**

### **4.1 Disposition of the study population**

A CONSORT diagram (see Appendix 1) will be produced showing a clear account of all practices and patients who entered the trial- see below for an example figure. Withdrawal information including the primary reasons of discontinuation will be summarised and presented by where this is known.

### **4.2 Protocol deviations**

A listing of all Major or Potential/Serious Breach (Major protocol deviations with potential to affect patient safety/data) and Potential/Serious Breach (with actual affect to patient safety/data, Major/Potential/Serious Breach of GCP guidelines or consistent non-compliance by site) will be produced (by patient and site where applicable)

### **4.3 Baseline and demographic characteristics**

Summary statistics will be produced and presented by group for demographic and baseline characteristics but no comparisons will be undertaken, rather the clinical importance of any imbalance will be noted. If there are imbalances of clinical importance in variables not listed in 4.4 below, we will control for these as covariates in the analyses.

### **4.4 Primary endpoint**

The primary outcome, that is, the differences at 6 months between intervention and control in depression as measured by the PHQ-9, will be analysed using a linear mixed model, adjusting for duration of depression, past history of depression, age, gender, marital status, no. of dependents, ethnic group, education level, economic position (employment status), and accommodation status, baseline depression score, anxiety score, internet use and clustering, including practice as a random effect. These covariates have been chosen based on their known relationship with the outcome from previous literature.

The model will use all the observed data and makes the assumption that missing PHQ-9 scores are missing completely at random. We will examine the lower limit of the 95% confidence interval to establish non-inferiority.

We will then undertake the same analyses using the per protocol population and the CACE population.

Whilst the ITT analysis will be the primary analysis, we will report the analyses based on all three approaches and interpret the findings cautiously in light of any differences between approaches that may emerge. This analysis will form the core of the publication of the trial results.

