### Randomisation

Randomisation will be computerised and carried out independently by the Southampton Clinical Trials Unit (SCTU). We will use the statistical technique of 'minimisation' to balance practice size (large/small), location (urban/rural), and social deprivation (dichotomised around the median Index of Multiple Deprivation (IMD) score). There is a random element to the minimisation algorithm, and so we might not expect perfect balance to the randomisation.

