## STATISTICAL ANALYSIS

Intention to treat (ITT) analyses at patient level will be performed, using mixed logistic/linear regression models, controlling for baseline values, stratification variables, and potential confounders as appropriate. Practice will be modelled as a random effect to allow for the clustering of patients within practices. Patterns of missing data will be explored, sensitivity analysis used to explore the impact of missingness, and imputation of missing data will be used. In a non-inferiority trial where some patients do not comply with treatment as randomised, the difference between the arms can appear reduced and the groups look more similar, leading to the incorrect conclusion of non-inferiority. A per protocol (PP) analysis would analyse individuals based on their compliance with treatment as randomised, excluding non-compliant participants, giving a more conservative estimate of effect for non-inferiority (Piaggio 2006).

However, the exclusion of some participants after randomisation can potentially lead to bias. Therefore we will present both ITT and PP analyses.

We will also undertake a complier-average causal effect (CACE) analysis, another approach to dealing with noncompliance that compares compliant participants in the intervention group, with those in the control group whose characteristics are similar enough to the intervention group compliers to suggest they too would have complied with the intervention, given the opportunity to do so (Angrist 1996, Dunn 2005). Compliance for these analyses in the intervention arm will be defined as completing the first session of the LifeGuide programme within 6 months of recruitment (anticipating 90% plus). The first session will have information about antidepressant treatment, the rationale for attempting withdrawal, and how withdrawal should be attempted under supervision. We would expect patients to benefit from that session even if they do not log on again. Compliance in the control arm will be defined as having consulted the GP/PN to have their antidepressant treatment reviewed within the 6-month follow-up period. For the primary outcome we will report the analyses based on all three approaches and interpret the findings cautiously in light of any differences between approaches that may emerge. This analysis will form the core of the publication of the trial results. No interim analyses will be performed.

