### **2.3 Randomisation details**

Randomisation of practices is by computerised sequence generation, and minimisation with a random element using three factors to avoid imbalance between the two arms: practice size (large/small), location (urban/rural) and social deprivation (dichotomised around the median Index of Multiple Deprivation score). The allocation ratio is 1:1 but there is a random element to the minimisation algorithm and so we might not expect perfect balance to the randomisation.

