### **4.5 Secondary endpoints**

The discontinuation of antidepressants will be evaluated at 6 months as a binary outcome in a mixed logistic regression model, using the same modelling approach and covariates as for the primary outcome.

Analysis of all other secondary outcomes will also be conducted using generalised linear mixed regression models adjusting for stratification variables, the potential confounders listed in 4.4 above and the baseline value of the outcome. These will be evaluated as repeated measures so all models will allow for the clustering of observations within participants over time and of participants within practices.

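### The primary PHQ-9 model in SAP 4.4 leaves out the three minimisation factors (a small, conservative loss), and SAP 4.3 lets other covariates enter after a by-arm look with no threshold

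*Combined protocol and SAP*

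**What the plan says.** SAP 2.3 allocates practices by "minimisation with a random element using three factors to avoid imbalance between the two arms". The factors are practice size, urban/rural location and deprivation split at the median. The protocol's Randomisation section names the same three, and neither document mentions any other allocation factor.

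The protocol's Statistical Analysis section describes mixed models "controlling for baseline values, stratification variables, and potential confounders as appropriate".

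SAP 4.4 lists the covariates of the primary model one by one: "adjusting for duration of depression, past history of depression, age, gender, marital status, no. of dependents, ethnic group, education level", then employment and accommodation status, and finally "baseline depression score, anxiety score, internet use and clustering, including practice as a random effect". That makes thirteen patient-level covariates and a practice random effect. None of the minimisation factors appears. The per-protocol and CACE analyses repeat this model, and SAP 3.3.2 takes the covariates of its imputation model from the analysis model.

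SAP 4.5 analyses discontinuation "using the same modelling approach and covariates as for the primary outcome". For all other secondary outcomes it specifies models "adjusting for stratification variables, the potential confounders listed in 4.4 above and the baseline value of the outcome".

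SAP 4.3 tabulates baseline characteristics by arm without formal comparison, and then states: "If there are imbalances of clinical importance in variables not listed in 4.4 below, we will control for these as covariates in the analyses".

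**The concern.** There are two separate issues.

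The first is an inconsistency. SAP 4.5 names the stratification variables in addition to the 4.4 list, which confirms that the 4.4 list does not contain them. PHQ-9 therefore has two adjustment sets: the 6-month primary analysis without the factors, and the 12-month repeated-measures analysis with them. No reason is given. When allocation has been balanced on a prognostic factor and the model ignores it, the reported standard error still carries variation that the design has removed. The interval is then wider than it need be.

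The second is the 4.3 rule. It gives no threshold for clinical importance, no list of candidate variables and no blinding of whoever judges, and it does not confine the result to sensitivity analyses. The primary result rests on one confidence limit set against a 2-point margin. A rule that lets the primary model change after the arms have been seen side by side sits poorly with SAP 1.1, which says the plan exists to prevent post hoc decisions. It also selects on imbalance, whereas 4.4 selects on known relationship with the outcome.

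**Working it through.** **Inputs.** From protocol Sample size calculation and SAP 2.2: margin 2, SD 5.4, one-sided alpha 2.5%, power 90%, mean cluster size 3, coefficient of variation 0.5, ICC 0.012, 20% non-compliance and/or loss, target 360, baseline correlation 0.47 (95% CI 0.26 to 0.63).

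**Reproducing the plan.**
- Per arm: 2 × (5.4 × (1.960 + 1.282) / 2)² = 153.2, so 154. The plan says 155, which is close enough.
- Design effect: 1 + ((1 + 0.5²) × 3 − 1) × 0.012 = 1.033, as stated.
- Total: 155 × 2 × 1.036 / 0.8 = 401.5, so 402. With 1.033 it is 400.3; the difference has no bearing here.
- After the revision: 402 × (1 − 0.26²) = 375 and 402 × (1 − 0.47²) = 313, as stated.

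None of these figures depends on the minimisation factors.

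**Most the factors could contribute.** Size, location and deprivation are properties of the practice, so they can explain only between-practice variance. Under the plan's ICC that is 1.2% of PHQ-9 variance. The design effect splits into a within-practice part, 1 − 0.012 = 0.988, and a between-practice part, 0.012 × 3 × 1.25 = 0.045, which sum to 1.033. If the factors explain a share f of the between-practice variance, the design effect becomes 0.988 + (1 − f) × 0.045.

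With all of the 20% treated as lost, 360 × 0.8 / 2 = 144 per arm. At correlation 0.26:

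SE = 5.4 × √(2/144 × design effect × (1 − 0.26²)), and power = Φ(2/SE − 1.96).

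| Share f (assumed) | Design effect | SE | SE reduction | Power |
|---|---|---|---|---|
| 0 (factors omitted, or not prognostic) | 1.033 | 0.6246 | none | 89.3% |
| 1/4 | 1.022 | 0.621 | 0.5% | 89.6% |
| 1/2 | 1.011 | 0.618 | 1.1% | 89.9% |
| 1 (ceiling) | 0.988 | 0.611 | 2.2% | 90.6% |

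The power column treats the reported SE as the sampling SD, which is an approximation. At correlation 0.47 the power without the factors is already 93.9%.

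**Direction.** A simulation used 134 practices of three patients, minimisation on three binary factors with an assumed 0.8 biased coin, regression on practice means, a true difference equal to the margin, and 3,000 runs per scenario.

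| PHQ-9 variance due to the factors (assumed) | One-sided error, omitted | One-sided error, included | Mean SE, omitted | Mean SE, included |
|---|---|---|---|---|
| 0% | 0.025 | 0.024 | 0.543 | 0.543 |
| 1% | 0.026 | 0.027 | 0.550 | 0.543 |
| 2% | 0.021 | 0.024 | 0.555 | 0.539 |
| 5% | 0.018 | 0.026 | 0.570 | 0.531 |
| 10% | 0.014 | 0.026 | 0.594 | 0.516 |

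Simulation error is about √(0.025 × 0.975 / 3000) = 0.003. The last three rows lie above the 1.2% that the plan's ICC allows, so they show the direction only. At 1% the two error rates cannot be told apart. Omission does not raise the false-claim rate in any row beyond simulation error.

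**SAP 4.3 rule.** Adding a covariate shifts the estimate by roughly imbalance × partial correlation × SD. For a 0.2 SD imbalance and an assumed partial correlation of 0.05 to 0.15, after the thirteen covariates in 4.4, the shift is 0.2 × 0.05 × 5.4 = 0.05 to 0.2 × 0.15 × 5.4 = 0.16 points, or 3% to 8% of the margin. A 0.2 SD imbalance is itself 0.2 / √(2/144) = 1.7 standard errors.

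**The case against.** The case for leaving the plan alone has substance.

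- The protocol qualifies its adjustment set with the words as appropriate and defers detail to a later plan, so a reader who infers a broken promise goes too far. This stands. It does not explain why adjustment would suit the repeated-measures PHQ-9 but not the 6-month PHQ-9. A drafting slip in 4.4 is quite possible.
- The model keeps practice as a random effect and adjusts for education, employment and accommodation, which may overlap with deprivation. This stands as a reason to expect a small gain. A random effect handles clustering but does not replace fixed effects for the allocation factors.
- A minimisation factor could still enter through 4.3. That would require it to be judged imbalanced, which minimisation makes unlikely.
- The 4.3 rule is written in advance, uses baseline data only and rejects between-arm testing. Practices are randomised before patients consent, so recruitment could differ by arm, and wanting to adjust for that is legitimate. This stands, and statisticians could differ on the rule. It does not settle why an adjustment with no threshold should alter the primary model when a sensitivity analysis would serve.

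A reader might also infer that both main results lose precision. Discontinuation is a secondary endpoint, and the linear standard-error argument does not carry over to its mixed logistic model, where adding prognostic covariates changes the odds ratio being estimated. No figure is offered for it.

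**Conclusion.** The inconsistency is real: none of the three minimisation factors is in the primary model, against the protocol's general statement and SAP 4.5. Its effect is small and conservative. For an assumed quarter to half of between-practice variance, it costs about 0.5% to 1.1% in standard error, or 0.3 to 0.6 points of power (89.3% against 89.6-89.9%). The ceiling is 2.2%, with power of 90.6%. If the factors are not prognostic, nothing is lost. These figures rest on the plan's ICC of 0.012, 144 followed up per arm and correlation 0.26; a larger true ICC would raise the ceiling.

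Three stronger readings are not supported. Omission does not make a false non-inferiority claim more likely. The factors cannot explain 2% to 5% of PHQ-9 variance while the ICC is 1.2%. Nor can the 4.3 rule be credited with moving the estimate by 0.2 × 0.3 × 5.4 = 0.32 points, 16% of the margin: that uses an assumed marginal correlation of 0.3, when the smaller partial correlation is what counts. Such a shift would in any case correct a chance imbalance, so it is not in itself a bias.

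The 4.3 rule is a lesser point: specified in advance, but loose enough to leave the primary model undetermined until the arms have been viewed.

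**What to change.** Add practice size, urban/rural location and deprivation, coded as in the minimisation, as fixed effects to the SAP 4.4 model. The discontinuation, per-protocol and CACE analyses and the imputation model then take them up through their existing cross-references, and 4.4 agrees with 4.5 and the protocol.

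Replace the last sentence of SAP 4.3 with a statement that the primary model is fixed as listed in 4.4, and that adjustment for any other observed baseline imbalance will be reported as a sensitivity analysis.

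The cost is two SAP edits and three practice-level degrees of freedom. The factors were recorded for allocation, so no new data are needed, and no stated sample size changes.

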### **2.2 Trial power and sample size**

To have 90% power, with a one-sided alpha of 2.5%, to establish non-inferiority in terms of depressive symptoms within two points (estimated to be the minimal clinically important difference) on the PHQ-9 at 6 months (standard deviation 5.4), we need 155 patients followed up in each arm. Assuming a variable cluster size of between 1 and 7 per practice (mean 3) and an intra-cluster correlation coefficient of 0.012 (from the Health Technology Assessment THREAD trial of treating mild-to-moderate depression in primary care), gives a 1.033 cluster design effect (based on a coefficient of variation of  $1.5/3 = 0.5$ , using the formula of Eldridge). Anticipating 20% do not comply with the intervention and/or are lost to follow-up, we need to randomise  $(155 \times 2 \times 1.036) / 0.8 = 402$  patients (201 per arm) from 134 practices (67 per arm).

Following discussion with the study steering committees and the funder, the sample size was amended to 360 participants. This allows for a correlation between baseline and follow-up scores with a deflation factor of  $1 - \rho^2$ . At the time of review we observed a correlation of 0.47 but were unsure whether this would persist to the end of follow up for all participants. If we assume the more conservative estimate of correlation of 0.26 (the bottom end of the CI), the target sample size to achieve 90% power would 375. We assume the final figure will be somewhere in between 0.26 and 0.47, and that a sample of around 360 will therefore provide us with the necessary 90% power to test reliably for non-inferiority of the intervention in terms of depressive symptoms.

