### **3.3.2 Missing data**

The primary analysis will be of complete cases.

If more than 2 items in the PHQ-9 and the GAD7 have missing values, the total score will be missing. If one or two items are missing, the score will be imputed with the mean of the non-missing scores before summing.

We will examine the structure and pattern of missing data and, if appropriate, will present a sensitivity analysis based on data imputed using a chained equations multiple imputation model. The imputation model would include the outcome measure, baseline value of the outcome, randomisation group, clustering by practice and all covariates included in the analysis model (see below)

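### The complete-case primary model drops a patient with an observed 6-month PHQ-9 if any of 13 baseline covariates is blank; the SAP should keep such patients by a stated rule.

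*Combined protocol and SAP*

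**What the plan says.** SAP 4.4 (Primary endpoint) specifies a linear mixed model for the 6-month PHQ-9, "adjusting for duration of depression, past history of depression, age, gender, marital status, no. of dependents, ethnic group, education level, economic position", then accommodation status, baseline depression score, anxiety score and internet use. That makes 9 + 4 = 13 patient-level covariates, with practice as a random effect. The section says the model draws on all observed data; the only missingness assumption it states concerns PHQ-9 scores.

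SAP 3.3.2 (Missing data) says "The primary analysis will be of complete cases". SAP 3.1.1 describes the modified ITT population as the patients as randomised, with nothing imputed. For the PHQ-9 and GAD-7, one or two blank items are replaced by the mean of the answered items. Chained-equations multiple imputation, including all the model covariates, is offered as a sensitivity analysis if judged appropriate. The protocol's Statistical Analysis section is firmer: it says imputation will be used.

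SAP 2.2 inflates the sample size thus: "Anticipating 20% do not comply with the intervention and/or are lost to follow-up". SAP 4.5 carries the same covariates into the secondary models, and SAP 4.3 allows more to be added for clinically important imbalance.

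**The concern.** Under complete-case rules a regression model uses only rows in which the outcome and every covariate are present. A patient followed up successfully at 6 months leaves the primary analysis because, for example, the accommodation question was left blank at baseline. Most of the 13 covariates are sociodemographic answers with no rule for a blank.

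Two things are at stake. The primary set can be smaller than the set of randomised patients with an observed outcome, for a reason unrelated to follow-up. And the confidence interval for the arm difference widens, which makes the 2-point margin harder to meet. The sample size allowance does not name this loss. Because the SAP does not address blank covariates explicitly, it also leaves room for a choice after the data are seen, which SAP 1.1 says the plan is meant to prevent.

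**Working it through.** **Inputs from SAP 2.2.** Design target: "To have 90% power, with a one-sided alpha of 2.5%, to establish non-inferiority in terms of depressive symptoms within two points". SD 5.4, giving 155 per arm with follow-up. Cluster sizes average 3 (range 1 to 7), coefficient of variation 0.5. ICC 0.012, allowance 20%, amended total 360. The observed baseline to follow-up correlation is 0.47, with 95% interval 0.26 to 0.63 (protocol, Sample size calculation). True difference taken as 0.

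**Reproducing the plan's figures.**
- n per arm = 2 × [5.4 × (1.960 + 1.282) / 2]² = 153.2, so 154; the t-based calculation gives 155 (90.2% power). Agrees with 155.
- Design effect = 1 + [(0.5² + 1) × 3 − 1] × 0.012 = 1.033. Agrees.
- Total = 155 × 2 × 1.036 / 0.8 = 401.5, so 402. Agrees.
- 402 × (1 − 0.26²) = 374.8 and 402 × (1 − 0.47²) = 313.2. These agree with 375 and 313.
- 360 corresponds to a correlation of √(1 − 360/402) = 0.32.

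**Share of observed outcomes lost (assumption).** The documents give no rate of blank covariates. With a proportion q blank in each of 13 covariates, independently, the share lost is c = 1 − (1 − q)^13:
- q = 0.5%: c = 6.3%, or 18 of 360 × 0.8 = 288 patients.
- q = 1%: c = 12.2%, or 35 of 288.

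**Power at 360.** Effective n per arm = 360 × 0.8 × (1 − c) / (2 × 1.033). SE = 5.4 × √(1 − ρ²) × √(2/n). Power = Φ(2/SE − 1.96).

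| Loss c | Effective n per arm | Power, ρ = 0.26 | Power, ρ = 0.47 |
|---|---|---|---|
| 0 | 139.4 | 89.3% | 93.9% |
| 6.3% | 130.6 | 87.3% | 92.4% |
| 12.2% | 122.3 | 85.1% | 90.7% |

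Using 1.036 in place of 1.033 leaves the whole percentages unchanged. The interval widens by 1/√(1 − c): 3.3% at c = 6.3% and 6.8% at c = 12.2%.

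**Slack before power drops below 90%.** At ρ = 0.26 there is none. At ρ = 0.325, close to what 360 implies, it is 1.7% of observed outcomes (about 5 of 288). At ρ = 0.47 it is 14.3% (about 41 of 288).

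**The case against.** The case for a smaller problem is strong on size.

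- No missingness rate is documented, so every loss figure is hypothetical. A reader might infer that the stated 90% power is in fact eroded. The documents do not support that: at the observed correlation of 0.47, power stays at or above 90% until about 14% of observed outcomes are lost.
- The calculation treats the whole 20% as absent, but ITT keeps non-compliers who supply a 6-month PHQ-9. If half of the 20% were such patients (assumption), 324 outcomes would be observed. At q = 1%, 324 × 0.99^13 = 284 would remain, with power 88.9%, 90.1% and 93.6% at correlations 0.26, 0.325 and 0.47, close to the plan's starting point. Variance explained by the other 12 covariates is also left out.
- Thirteen equally exposed, independent covariates is near a worst case. PHQ-9 and GAD-7 are collected at screening and again at baseline, a researcher conducts the baseline assessment, and blanks tend to fall in the same patients. With nine exposed covariates (assumption) the loss is 4.4% at q = 0.5% and 8.6% at q = 1%.
- The sentence about using all observed data sits beside the PHQ-9 missingness assumption. A reader might call it untrue; more exactly, it conflicts with the complete-case rule whenever a covariate is blank.
- A wider interval works against declaring non-inferiority. Nothing here shows bias or a raised risk of a false claim.

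All of this limits the size. It does not remove the exclusion. The item rule covers two of the 13 covariates, and the planned imputation is conditional and not primary.

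**Conclusion.** The point stands as a defect in the primary analysis rule, with an effect on precision that may be small. Read together, SAP 3.1.1, 3.3.2 and 4.4 discard observed primary outcomes for blank baseline answers, and they sit uneasily with the protocol's commitment to imputation and with SAP 4.4's own statement about observed data.

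On the plan's parameters, independent blanks of 0.5% to 1% per covariate would cost about 2 to 4 percentage points of power at correlation 0.26, and about 1.5 to 3 at 0.47. That rests on an assumed missingness rate, on independence across covariates, and on the full 20% being lost. It should not be read as a demonstrated loss of power, nor as evidence of bias. The change is worth making because it is cheap and retains outcomes already collected.

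**What to change.** Amend SAP 3.3.2 and 4.4 to say that every patient with a 6-month PHQ-9 enters the primary linear mixed model. Missing baseline covariates are filled in without regard to arm: a separate 'not stated' category for categorical covariates, and the mean pooled over both arms for continuous ones. The protocol's Consent procedure has patients complete baseline before they learn their arm, so blanks should not be driven by patients' knowledge of allocation, and an arm-blind fill-in should not bias the arm difference in the linear model. Make complete-case on covariates a sensitivity analysis.

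Reconcile SAP 3.1.1 and 3.3.2 with the protocol's Statistical Analysis section and with SAP 4.4, making clear that the fill-in concerns baseline covariates and that the outcome is not imputed in the primary analysis.

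The same rule can serve the secondary models, with one caveat. In the logistic model for discontinuation, weaker covariate adjustment can move the conditional odds ratio slightly toward 1, so a reader should not assume that the arm effect is untouched in every model.

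Cost: one SAP paragraph, a few lines of code, and slightly attenuated covariate coefficients.

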## **3.4 Definition of key derived variables**

The PHQ-9 is a self-complete questionnaire taking approximately 3 min to complete. Each item is scored 0-3 with a total possible score ranging from 0-27. Higher scores indicate more severe symptoms.

The Generalised Anxiety Disorder Assessment 7-item version is a self-report measure of anxiety symptoms. Each item is scored from 0-3 with a total possible score ranging from 0-21. Higher scores indicate more severe symptoms.

Discontinuation of antidepressants is deemed to have occurred once the patient has stopped taking them for 2 months. This is a binary outcome (did not discontinue/did discontinue).

The Warwick–Edinburgh Mental Wellbeing Scale (WEMWBS) measures both subjective experiences of happiness and life satisfaction (the ‘hedonic perspective’), and positive psychological functioning, good relationships with others and self-realisation (the ‘eudaimonic perspective’). Each item is answered on a 1 to 5 Likert scale and summed to give a total score ranging from 14 to 70. Higher scores indicate greater wellbeing.

Antidepressant withdrawal symptoms are measured using the Discontinuation Emergent Signs and Symptoms scale, a brief self-report measure on which participants can indicate the presence of, and

changes in, 43 possible antidepressant withdrawal symptoms. The total number of symptoms is summed.

The 29-item 'Medical Interview Satisfaction Scale' (MISS-29) was developed in the USA to assess patient satisfaction with individual doctor-patient consultations and has been shown to be valid and reliable in UK primary care.

The modified Patient Enablement Instrument asks 6 questions about the patients' ability to understand their problems and cope with illness. These are rated on a 7 point Likert scale (0=strongly agree to 7=strongly disagree). A mean overall score can be calculated, with lower scores equating to better enablement.

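### SAP 4.4 bases the primary non-inferiority decision on the lower confidence limit without defining the difference, the signed margin or the threshold; under intervention-minus-control coding that is the wrong limit

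*Combined protocol and SAP*

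**What the plan says.** SAP 4.4 describes the primary comparison as "the differences at 6 months between intervention and control in depression as measured by the PHQ-9", estimated from a linear mixed model. The decision rule is one sentence: "We will examine the lower limit of the 95% confidence interval to establish non-inferiority". No order of subtraction, signed margin or comparison value is attached to it. The same analyses are then to be run in the per-protocol and CACE populations.

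Three other parts of the SAP bear on how that sentence should be read:

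- **SAP 3.4** on PHQ-9: "Each item is scored 0-3 with a total possible score ranging from 0-27. Higher scores indicate more severe symptoms".
- **SAP 2.2** gives the aim as "to establish non-inferiority in terms of depressive symptoms within two points", at one-sided 2.5% alpha and 90% power. The margin has no sign.
- **SAP 3.5** sets a "5% two-sided level of statistical significance, with corresponding 95% confidence intervals presented where applicable".

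The Statistical Analysis section of the protocol discusses intention-to-treat, per-protocol and CACE analyses for non-inferiority but names no confidence limit. Neither document defines the difference as control minus intervention, or as intervention minus control.

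**The concern.** A non-inferiority test has to rule out harm. On a scale where higher is worse, and with intervention minus control as the difference, harm lies in the positive direction. The limit that can rule it out is the upper one. The lower limit of that difference says how much better the intervention might be, and nothing about how much worse. Using the lower limit is the familiar convention for outcomes where higher is better, and PHQ-9 runs the other way.

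This sentence is the whole decision rule for the only primary endpoint, and it carries over to the two supporting analyses. The trial asks whether supported withdrawal from antidepressants leaves patients more depressed. If the rule is applied in the wrong direction, the primary conclusion does not answer that question. If the direction is chosen at analysis, a choice that decides the result is made after the fact, which SAP 1.1 says the plan exists to prevent.

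**Working it through.** **Inputs.** From SAP 2.2: margin 2 points, SD 5.4, one-sided alpha 2.5%, power 90%, 155 followed up per arm, design effect 1.033, 20% non-compliance or loss, 360 recruited after amendment, and a correlation of 0.26 (conservative) or 0.47 (observed at review). From SAP 2.3: 1:1 allocation.

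**Reproducing the plan's own figure.** With a true difference of zero,

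n per arm = 2 × [SD × (1.960 + 1.282) / margin]² = 2 × [5.4 × 3.242 / 2]² = 153.2, so 154.

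The plan states 155, which agrees closely. The planned test is therefore the ordinary one: exclude a 2-point worsening at one-sided 2.5%, which is the same as using one limit of a two-sided 95% interval.

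**Standard error at the amended size.** Followed up per arm: 360 × 0.8 / 2 = 144. Effective number: 144 / 1.033 = 139.4.

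SE = 5.4 × √(1 − 0.26²) × √(2 / 139.4) = 0.625; half-width of the 95% interval = 1.96 × 0.625 = 1.22.

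**Readings of the sentence.** Let D be the true intervention-minus-control difference, so that positive means the intervention is worse, and let the estimate be normal around D.

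- *Intended test:* upper limit of D below +2. Passes if the estimate is below 2 − 1.22 = 0.78.
- *Reading A:* lower limit of D above −2. Passes if the estimate is above −2 + 1.22 = −0.78.
- *Reading B:* lower limit of D below +2. Passes if the estimate is below 2 + 1.22 = 3.22.
- *Reading C:* difference coded control minus intervention, lower limit above −2. Changing the sign turns this into the intended test.

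Probability of concluding non-inferiority:

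| True D | Intended test and C | Reading A | Reading B |
|---|---|---|---|
| −2 | >0.999 | 0.025 | >0.999 |
| 0 | 0.893 | 0.893 | >0.999 |
| +2 | 0.025 | >0.999 | 0.975 |
| +3 | 0.0002 | >0.999 | 0.640 |
| +4 | <0.001 | >0.999 | 0.107 |
| +5 | <0.001 | >0.999 | 0.002 |

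Reading A passes harm of any size shown and fails an intervention that lowers PHQ-9 by 2 points 97.5% of the time. Reading B passes anything not shown to be worse than the margin.

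**Sensitivity.** The 2.5% and 97.5% at D = +2 do not depend on the standard error, because they are Φ(−1.96) and Φ(+1.96). With 155 per arm and no adjustment for correlation or clustering (SE 0.613), B gives 0.629 at +3 and the intended test 0.903 at zero. With 144 per arm, design effect 1.033 and correlation 0.47 (SE 0.571), the figures are 0.583 and 0.939. Reading A stays above 0.999 at +2 in each case.

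**The case against.** The strongest reply is that the SAP never says intervention minus control. With control minus intervention and a margin of −2, the lower limit is correct, error at the margin is 2.5%, and the sentence is the planned test. The surrounding text also shows what was meant. SAP 2.2 gives the margin and one-sided alpha, SAP 3.4 gives the direction of the scale, SAP 1.2 frames success as less antidepressant use without depression getting worse, and SAP 1.5 commits to the CONSORT extension for non-inferiority trials. Readings A and B are not written in the SAP, and neither matches a one-sided 2.5% hypothesis of no material worsening. Leaving the margin out of 4.4 is not itself an error, since 2.2 gives it.

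Much of this stands. A reader might infer that the SAP has adopted the wrong limit outright, that a harmful intervention would be declared non-inferior, or that type I error control has been lost. The documents do not support those statements. Each depends on an order of subtraction that no section supplies, and the size of the damage also depends on an unstated threshold: under Reading B a true difference of +5 passes only 0.2% of the time.

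The reply does not make the sentence sound. Intervention is named first in 4.4, and intervention minus control is the usual coding. Under it the named limit cannot exclude harm. The passages that show the intent do not settle the sign, so the correct test has to be inferred against the usual reading of the one sentence that states the rule.

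**Conclusion.** The point holds conditionally. SAP 4.4 names a specific limit for the primary decision and leaves the direction of the difference, the sign of the margin and the threshold undefined. Under intervention-minus-control coding it is the wrong limit, and a true 2-point worsening would pass 97.5% of the time (Reading B) or more than 99.9% (Reading A), against 2.5% planned. At +3 the figures are 64% and more than 99.9%, against 0.02% for the intended test. Under control-minus-intervention coding with a margin of −2 the rule is correct.

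The figures assume a normal estimate, 360 recruited, 20% loss, design effect 1.033, SD 5.4 and correlation 0.26. The results at the margin hardly depend on these inputs. This goes beyond a missing detail, because the limit that is named gives a wrong primary conclusion under the usual coding and nothing elsewhere corrects it.

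**What to change.** Replace the sentence in SAP 4.4 with:

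*The difference is adjusted mean PHQ-9 at 6 months, intervention minus control; non-inferiority is concluded if the upper limit of the two-sided 95% CI is below +2.0 points.*

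State that the same rule applies to the per-protocol and CACE analyses. The mirror form would serve equally well if written out in full: control minus intervention, lower limit above −2.0. The direction should be fixed before anyone sees the comparison between arms.

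The cost is one sentence in the SAP. Sample size and alpha do not change, because the upper limit of a two-sided 95% interval is the one-sided 2.5% test already used in SAP 2.2.
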